## Abstract

**Introduction:** Chronic heart failure (CHF) is a common cardiovascular disease. In China, Xinbao pill (XBP) is widely used as an adjuvant therapy for CHF. However, there is still a lack of high-quality clinical evidence. We designed this multicenter, randomized, double-blind, placebo-controlled trial to critically evaluate the efficacy and safety of XBP as an adjuvant treatment for patients with CHF.

**Methods and analysis:** We will recruit 284 patients with a clinical diagnosis of “heart-kidney yang deficiency syndrome” CHF receiving treatment in six hospitals in China. Patients will be randomly assigned, in a 1:1 ratio, to the treatment or control group using a central randomization system. All patients will receive conventional drug therapy for heart failure combined XBP (Guangdong Xinbao Pharmaceutical Co., Ltd., Guangdong, China) or a placebo. Study physicians, subjects, outcome assessors, and statisticians will be blinded to the group assignment. The primary outcome will be the change in the proportion of patients who show a decrease in serum NT-proBNP of more than 30% after treatment. Secondary outcomes are NYHA class, 6-minute walk distance test, Minnesota Quality of Life Scale score, endpoint events, serum NT-proBNP, echocardiographic parameters, and traditional Chinese medicine (TCM) symptom score. Adverse events will be monitored throughout the trial. Data will be analyzed according to a predetermined statistical analysis plan.

**Discussion:** The results of this study will provide solid evidence of the safety and efficacy of XBP as an alternative and complementary treatment measure for patients with CHF.

**Clinical Trial Registration:** Chinese Clinical Trial Registration Center (ChiCTR2000038492).

## Introduction

Chronic heart failure (CHF), an end-stage of various cardiac functional/organic diseases, is a major public health problem facing the world (Francis, 2001). Epidemiological data show that approximately 64.3 million people worldwide are afflicted by this disease (Groenewegen et al., 2020). In developed countries, the prevalence of heart failure is generally estimated at 1%–2% of the general adult population (Hao et al., 2019). As the population continues to increase in age, the prevalence of CHF is on the increasing, and it is estimated that by 2030, the prevalence of heart failure in the United States alone will increase by 46%, totaling more than eight million cases (Mozaffarian et al., 2016). In the United States, CHF is the leading cause of hospitalization for people older than 65 years of age, accounting for approximately one million hospitalizations each year (Rosamond et al., 2008), placing a tremendous burden on the individual and the health care system (Roger, 2021). The angiotensin-converting enzyme inhibitor (ACEI)/angiotensin receptor neprilysin inhibitor (ARNI), sodium glucose cotransporter two inhibitor, a beta-blocker, and mineralocorticoid receptor antagonists (MRA) are currently recommended in the guidelines as the basic therapy for CHF (McDonagh et al., 2021). Nevertheless, the prognosis of patients with CHF is not good. Studies have shown that the mortality rate of CHF patients within 1 month of discharge after receiving systemic and conventional basic treatment is still as high as approximately 10% (Pfeffer et al., 2019).

The Xinbao pill (XBP), a well-known Chinese patent medicine, was developed by Guangdong Xinbao Pharmaceutical Co., Ltd. (Guangdong, China) and approved by the China Food and Drug Administration (No: Z44021843) for the treatment of CHF. XBP is composed of nine herbal extracts (Table 1) and has been widely used in China in recent years for the treatment of cardiovascular diseases, especially for CHF. To explore the potential mechanism of XBP in the treatment of CHF, researchers have conducted a meaningful exploration. Previous studies have shown that in a rat model of CHF induced by abdominal aortic constriction surgery, XBP ameliorated the pathological changes of myocardial hypertrophy, disturbed cardiomyocyte arrangement and gap widening in CHF rats, and enhanced cardiac function (He et al., 2020). The mechanism might be related to the inhibition of phosphorylation activation of PI3K/Akt signaling and inhibition of GSK3β phosphorylation (He et al., 2020). It has also been shown that in a rat model of left anterior descending ligation-induced myocardial ischemia‒reperfusion injury, XBP could improve cardiomyocyte apoptosis by inhibiting autophagy and ER stress to improve cardiac function (Yang et al., 2022). The efficacy of XBP for CHF has also been demonstrated in clinical practice (Xu and Qi, 2019). However, it is disappointing that the evidence from these clinical randomized controlled trials is inadequate and shows significant methodological flaws, such as prevalent use of small samples, lack of preregistered study protocols, unreasonable random assignment methods, failure to implement blinding, and single-center studies (Wang et al., 2022).

**TABLE 1 T1:** Components of Xinbao pill (intervention drug).

Scientific name	Chinese Pinyin	Chinese Name	Latin scientific name	Part & form used
*Moschus (the dried preputial secretion of Moschus berezovskii, M. sifanicus or M. moschiferus)*	She Xiang	麝香	Moschus	the dried preputial secretion of Moschus berezovskii
Panax ginseng C. A. Meyer	Ren Shen	人参	Panax ginseng C. A. Meyer	Dried root
*Cinnamomum verum J. Presl [Lauraceae]*	Rou Gui	肉桂	Cinnamomum cassia Presl	Dried bark
*Datura metel L. [Solanaceae]*	Yang Jin Hua	洋金花	Dature Stramonium Datura L	Dried flower
*Aconitum carmichaeli Debeaux [Ranunculaceae]*	Fu Zi	附子	Aconiti Lateralis Radix Praeparata	Root
*Panax notoginseng (Burkill) F.H.Chen [Araliaceae]*	San Qi	三七	Panax notoginseng (Burkill) F. H. Chen ex C. H.	Dried roots and rhizomes
*Bufonis Venenum*	Chan Su	蟾酥	Bufo bufo gargarizans Cantor	the dry secretion of Bufo bufo gargarizans Cantor or Bufo melanostictus Schneider
*Cervi Cornu Pantotrichum*	Lu Rong	鹿茸	Cervus nippon	the unossitized, densely hairy young horn of a buck by Cervus Nippon Temminck or Cervus elaphus Linnaeus
Cinnamomum camphora (L.) J. Presl	Bing Pian	冰片	Borneolum Syntheticum	-

The clinical efficacy and safety of XBP in the treatment of CHF is still unclear. Therefore, we conducted a multicenter, randomized, double-blind, placebo-parallel controlled trial to try to elucidate the clinical efficacy and safety of XBP in the treatment of CHF, to provide high-quality evidence-based medical evidence. The main hypothesis of this study is that XBP is superior to placebo in patients with CHF when combined with conventional therapy.

## Methods and analyses

### Design and settings

This study is a multicenter, stratified, randomized, double-blind, placebo-controlled, parallel-group superiority trial planned to be implemented in patients with CHF with “heart-kidney yang deficiency syndrome.” A total of 284 participants will be recruited. After participants are enrolled and provided written informed consent, they will be randomly assigned, in a 1:1 ratio, to either the XBP group or the placebo group. The trial will consist of a 1-week screening period, 12-week intervention period, and 12-week follow-up period. The study flow is shown in Figure 1.

**FIGURE 1 F1:**
[figure not shown]
The flow diagram of this study.

## Recruitment

Announcements and recruitment advertisements will be posted on WeChat, hospital outpatient waiting halls and community bulletin boards for participant recruitment. Researchers will explain the purpose of the study, the interventions, and the benefits and risks to the patients. Patients who agree to participate will be examined and diagnosed separately by two chief Chinese medicine practitioners with more than 5 years of medical experience to determine whether they meet the inclusion criteria and will be enrolled in the online allocation system after written informed consent is obtained. In addition, the demographic characteristics of ineligible patients and reasons for nonparticipation will be recorded. Enrollment begins from 1 November 2020 to 31 December 2024. Costs incurred in connection with the study will be free of charge (e.g., physical examination, laboratory test costs, *etc.*). Recruitment will be conducted at six centers nationwide, including Shunde Hospital of Guangzhou University of Chinese Medicine, Er sha Branch of Guangdong Provincial Hospital of Chinese Medicine, University City Branch of Guangdong Provincial Hospital of Chinese Medicine, Second Guangdong Provincial Hospital of Chinese Medicine, Shandong Provincial Hospital of Chinese Medicine, and Huizhou City Hospital of Chinese Medicine.

## Eligibility criteria

### Diagnostic criteria of CHF

The diagnostic criteria were referenced in the 2018 Chinese Heart Failure Diagnosis and Treatment Guidelines published by the Chinese Medical Association Cardiovascular Disease Branch (Group et al., 2018). Among them, the grading of the severity of cardiac function is based on the New York Heart Association (NYHA) cardiac function grading criteria (Yancy et al., 2013). NYHA Class I: the patient has heart disease, but physical activity is not limited. General physical activity does not cause excessive fatigue, palpitations, shortness of breath, or angina; Class II: The patient has heart disease such that physical activity is mildly restricted. No symptoms at rest, general physical activity causes excessive fatigue, palpitations, shortness of breath or angina; Class III: The patient has heart disease such that physical activity is significantly limited. No symptoms at rest, but less than general physical activity can cause excessive fatigue, palpitations, shortness of breath or angina; and Class IV: Patients with heart disease, also have symptoms of cardiac insufficiency or angina at rest, and any physical activity increasing discomfort.

### Diagnostic criteria of traditional Chinese medicine syndrome

The diagnostic criteria for “heart-kidney yang deficiency syndrome” are based on the Expert Consensus on CHF Treatment in Chinese Medicine (Alliance et al., 2014). The main symptoms include palpitations, shortness of breath, weakness, shortness of breath with movement, cold body and limbs, puffiness and swelling, abdominal distension and loose stools, dull complexion, pale tongue with thin coating, sunken and weak pulse, or shortness of breath, astringency, and knotted generation. The diagnosis of “heart-kidney yang deficiency syndrome” is based on the presence of one primary symptom and two secondary symptoms. Two experienced chief physicians confirmed the “heart-kidney yang deficiency syndrome” diagnosis.

### Inclusion criteria

Patients will be included in this study if they meet the following criteria: 1) meet the diagnostic criteria for CHF, and the Chinese medical evidence of “heart-kidney yang deficiency syndrome”; 2) 18 years old ≤ age ≤80 years old, regardless of sex; 3) have a history of CHF for more than 3 months or clinical findings of heart failure symptoms for more than 3 months; 4) NYHA heart function classification II-III, or stable clinical symptoms, including those who have been diagnosed within 2 weeks before enrollment or NYHA Class IV; 5) serum N-terminal prohormone of brain natriuretic peptide (NT-proBNP) level ≥450 pg/ml; 6) have received conventional basic treatment for at least 2 weeks and have not undergone a dose adjustment; and 7) voluntary participation, clearly understanding and signed the informed consent form.

### Exclusion criteria

Patients who meet one of the following criteria will be excluded from this study.1) heart failure due to valvular disease, congenital heart disease, pericardial disease, arrhythmia and noncardiogenic causes, or heart failure due to liver, kidney and other important organ failure; and right heart failure and acute heart failure with clear pulmonary or other causes; 2) those who plan to undergo coronary revascularization therapy or cardiac resynchronization therapy in the near future, and those who have already undergone cardiac resynchronization therapy; 3) patients with severe primary diseases of the liver, kidney and hematopoietic system, liver transaminases, alkaline phosphatase exceeding 3 times the upper limit of the normal values, blood creatinine >2 mg/dl (176.82 μmol/L), blood potassium >5.5 mmol/L; patients with tumors, severe neuroendocrine disorders and psychiatric disorders; 4) patients with left ventricular outflow tract obstruction, myocarditis, large aneurysms, sandwich aneurysms, or unrepaired heart valves causing significant hemodynamic changes; 5) patients with cardiogenic shock, uncontrollable malignant arrhythmias, progressively worsening unstable angina pectoris or acute myocardial infarction; 6) patients with uncontrolled hypertension, systolic blood pressure ≥180/mmHg and/or diastolic blood pressure ≥110 mmHg; 7) patients who are also using other drugs with cardiotonic, or diuretic effects, such as digitalis; 8) patients who are taking other Chinese herbal medicines within 1 month; 9) pregnant or preparing for pregnancy and lactation; 10) allergic patients or those with a known allergy to the treatment drugs; 11) patients with internal heat of Yin deficiency, hyperactivity of the liver and Yang, or phlegm and fire; 12) patients with glaucoma; or 13) patients who, in the judgment of the investigator, cannot complete the study or cannot comply with the requirements of the study.

### Termination criteria

The clinical trial will be terminated if any of the following occur during the course of the trial.1) discontinuation of treatment at any time; 2) an allergic reaction clearly associated with the study drug; 3) an adverse sign or symptom (for example, vomiting, diarrhea, dizziness and headache, weakness, *etc.*) clearly associated with the study drug, or an abnormal test result that, in the judgment of the investigator, warrants discontinuation of the study; 4) pregnancy in a woman; 5) an endpoint event. When a trial is discontinued, all trial records should be retained for review.

### Withdrawal criteria

All screened and qualified subjects for entry into the trial who complete the informed consent form will not be affected by their subsequent treatment, regardless of when or why they withdraw from the study. Patients have the right to withdraw from the study at any time and for any reason, but every effort should be made to avoid unnecessary patient withdrawals and to complete follow-up visits whenever possible to collect data for analysis of efficacy and safety. However, when a patient decides to withdraw, the investigator should contact the patient or their responsible relative by telephone or personal visit and confirm the reason for withdrawal if possible. The investigator should retrieve the remaining medication at the time of withdrawal, perform complete a final assessment, complete a case report if possible, explain the reason for withdrawal, and follow up on the occurrence of the endpoint event in the withdrawing patient. If the patient withdraws for reason of an adverse event, it should be documented in the complete case report form (CRF).

### Sample size

Investigators conducting the trial estimate the sample size based on the level of NT-proBNP, the main efficacy indicator. The literature (Li et al., 2013), showed that NT-proBNP levels decreased by more than 30% after 12 weeks of conventional basic treatment combined with placebo in 31.98% of patients, and NT-proBNP levels decreased by more than 30% after 12 weeks of conventional basic treatment combined with herbal medicine in 47.95% of patients. Therefore, it is expected that the percentage of patients with NT-proBNP levels decreasing more than 30% after 12 weeks of conventional basic treatment combined with XBP will be 50%. Thus, assuming *α* = 0.05 and *β* = 0.20, the calculated sample size required for each group was 114 cases after substituting the above values using PASS11 software. Considering that 20% will miss visits, the sample size was adjusted to 142 cases in each group. The total number of cases required for both groups was 284.

### Randomization and allocation

Participants will be randomly assigned, in a 1:1 ratio, to the experimental and control groups using the central randomization system of the Drug Clinical Trial Management Office, Shunde Hospital of Guangzhou University of Chinese Medicine. Randomization groups will be stratified by the central stratification method, generating random numbers, and generating randomized results by SAS statistical software (version 9.4; SAS Institute, Cary, NC, United States). The randomization number and drug number will be separately obtained by each study subcenter investigator using a sequential number in the central randomization system. All center numbers, sequence numbers, randomization numbers, and drug numbers will be managed by the statistical unit.

### Blinding

Blinding codes will be made after the randomization operation. This process will be performed by a special person, and the sequence number of the subject, the corresponding random numbers and the grouping result (i.e., subjects are assigned to either the test or control group) will be the primary blinding base; then the two groups will be blinded to the medication, which will be the secondary blinding base, and the drug number of each subject will be randomly prepared in order, and all operations will be recorded and maintained. All study personnel, participants, physicians, medication administrators, and dispensing nurses will be unaware of the group and treatment type until the study is completed. Unblinding occurred if a participant have a serious adverse event during the course of the study or require emergency care in an emergency situation. Once unblinded, the participant will be withdrawn from the study and the investigator will report the reason to the examiner within 24 h.

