### Secondary outcome indicators

1) cardiac function classification (NYHA) (Yancy et al., 2013); 2) the 6-minute walking distance test (6MWT) (Ingle et al., 2005); 3) the Minnesota Living with Heart Failure Questionnaire score (Fitz et al., 2021); 4) the rate of endpoint events (acute exacerbation rehospitalization of CHF, cardiac death and all-cause death, *etc.*); 5) serum NT-proBNP level; 6) cardiac function indicators, such as the left ventricular ejection fraction (LVEF), the left ventricular end-diastolic diameter (LVEDD), and the left ventricular end-systolic diameter (LVESD); and 7) TCM symptom scores (Supplementary material 1) will be used to quantify the symptoms. Differences in TCM symptom scores between groups at baseline and week 4, week 8, week 12 and week 24 post-treatment will be compared and differences between groups will be calculated. The scoring process will be carried out independently by two chief TCM physicians with more than 5 years of medical experience, with any discrepancies being resolved through consultation. The comprehensive efficacy criteria were as follows: 1) ineffective: no significant improvement or even worsening of symptoms and signs, and a reduction in symptom score <30%; 2) effective: improvement of symptoms and signs, and a reduction in symptom score ≥30%; 3) significant effect: significant improvement of symptoms and signs, and a reduction of syndrome score ≥70%. TCM symptom scores = [(posttherapy score - pretherapy score)/pretherapy score]  ×  100%. Outcome indicators will be collected at week 4, 8, 12 and 24 after inclusion in the study.

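### The termination and unblinding rules take participants out of the study for outcome-related reasons, contradicting the withdrawal section's instruction to keep following them

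*Protocol article*

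**What the plan says.** Three sections of the protocol article bear on this.

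- **Termination criteria.** The list opens with "discontinuation of treatment at any time" and closes with "4) pregnancy in a woman; 5) an endpoint event". The lead-in speaks of ending the clinical trial, but the listed events make sense only for an individual participant. After discontinuation, the section asks only that records be kept.
- **Blinding.** "Unblinding occurred if a participant have a serious adverse event during the course of the study or require emergency care in an emergency situation". The consequence follows: "Once unblinded, the participant will be withdrawn from the study". The withdrawal is from the study, not only from study medication. The same section says that personnel and participants stay unaware of the allocation to the end of the study.
- **Withdrawal criteria.** Here "every effort should be made to avoid unnecessary patient withdrawals and to complete follow-up visits whenever possible to collect data for analysis of efficacy and" (the sentence goes on to name safety as well). The investigator is also to make a final assessment and to "follow up on the occurrence of the endpoint event in the withdrawing patient".

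Endpoint events are a secondary outcome, defined as "the rate of endpoint events (acute exacerbation rehospitalization of CHF, cardiac death and all-cause death" and so on. Table 3 assigns them a log-rank test. Table 2 schedules NT-proBNP and endpoint events at every visit through week 24. The primary outcome is the proportion of patients whose NT-proBNP falls by more than 30% after the 12-week course. Efficacy is analysed on a full analysis set (FAS) and a per-protocol set.

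**The concern.** The reasons for leaving the study are tied to how the patient is doing. A readmission for acute worsening is an endpoint event and so a termination criterion. If it involves emergency care, it also triggers unblinding and withdrawal. If a site acts on these rules before week 12, the primary measurement may never be taken in the patients with the worst course. An FAS can keep such a patient in the denominator, but it cannot recover a blood sample that was not drawn.

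The log-rank analysis has a similar problem. A patient removed after a serious adverse event that is not an endpoint, or after stopping treatment, is censored for a reason probably related to later risk. A death after a terminating readmission could also go unrecorded, although cardiac and all-cause death are both listed as outcomes.

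The sections also give conflicting instructions. One of the six centres could stop visits under the Termination criteria while another continues them under the Withdrawal criteria. Recruitment is under way, so what is not collected now is lost.

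**Working it through.** **1. The plan's own sample size.** Inputs from the Sample size section: 31.98% responders on placebo, 50% on XBP, alpha 0.05 and power 0.80. Tests are two-sided (Statistical analysis methods). With unpooled variance:

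n = (1.960 + 0.842)² × (0.3198 × 0.6802 + 0.50 × 0.50) / (0.50 - 0.3198)² = 113.01, so 114 per group.

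The pooled-variance form gives 116. The allowance for missed visits gives 114 / 0.80 = 142.5, against the stated 142. The stated figures reproduce within rounding and are not in dispute. They show that the plan expects up to 20% without a usable visit.

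**2. The rules side by side.**

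| Event before week 12 | Termination criteria / Blinding | Withdrawal criteria |
|---|---|---|
| Study treatment stopped | Participation ends | Complete visits where possible |
| Non-fatal endpoint event | Participation ends | Complete visits where possible; follow endpoint events |
| Unblinding after a serious adverse event or emergency care | Withdrawn from the study | Complete visits where possible; follow endpoint events |

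Each row gives two instructions, and the article does not say which prevails.

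**3. What removal could do to the primary comparison.** The documents give no removal rates, so all rates here are assumptions. Suppose there is no true effect: r = 31.98% responders among all randomised in each arm, 142 per arm. Suppose also that every removed patient is a non-responder and only those left are analysed. With a share w removed, the observed rate is r / (1 - w).

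| Removed, placebo v XBP | Observed, placebo v XBP | Shift, XBP minus placebo | Two-sided type I error | False win for XBP |
|---|---|---|---|---|
| 10% v 10% | 35.5% v 35.5% | 0 | 5.0% | 2.5% |
| 5% v 10% | 33.7% v 35.5% | +1.9 points | 6.2% | 5.0% |
| 10% v 20% | 35.5% v 40.0% | +4.4 points | 11.0% | 10.6% |
| 15% v 5% | 37.6% v 33.7% | -4.0 points | 10.1% | 0.4% |

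For example, 0.3198 / 0.80 - 0.3198 / 0.90 = 0.3997 - 0.3553 = 0.0444. Error rates use the pooled z test with 142 × (1 - w) patients per arm. The planned effect is 50 - 31.98 = 18.0 points.

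If a fraction q of removed patients would have responded, the observed rate is (r - wq) / (1 - w). For q between 0 and r, common to both arms, the shift shrinks as q rises and vanishes at q = r. The table is therefore the extreme case for its removal rates.

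**The case against.** The strongest reply is that the article never says these patients leave the primary comparison. The Withdrawal criteria ask for visits to be completed to support the efficacy analysis, Table 2 has NT-proBNP at each of those visits, and efficacy is analysed on an FAS. The 20% allowance is compatible with several ways of handling missing values. This stands. A reader might infer that the worst outcomes do drop out and that the trial will compare event-free completers, but the documents do not support that. They support a contradiction and a risk.

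Four further objections stand in part.

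- **Size and direction.** Equal removal produces no bias under the null, and the opposite imbalance works against XBP. A single unfavourable scenario would mislead, so a range is shown.
- **Later deaths.** A reader might infer that deaths after a first readmission are certainly lost. The Withdrawal criteria ask for endpoint follow-up, and a time-to-first-event log-rank test would not use such deaths anyway. The loss is possible, not established.
- **Unblinding.** The loosely worded sentence may describe when the code may be broken rather than a code break for every serious adverse event. It requires a reason to be reported, and the Adverse events section has no unblinding step. Even so, unblinding as described leads to withdrawal from the study.
- **Coding.** Counting removed patients as non-responders is a debatable choice that belongs in the SAP. If 31.98% and 50% apply to the other patients and removal is equal, power with 142 per arm is 81.2%, 77.6% and 73.7% at 10%, 15% and 20% removed. Leaving them out gives 83.8%, 81.6% and 79.3%.

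The Withdrawal criteria do not settle the matter. Their request is qualified by what is possible, a final assessment at withdrawal need not be a week-12 value, and two other sections say that participation ends.

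**Conclusion.** The concern holds as a contradiction in the conduct rules that carries a risk of informative missingness and informative censoring. It is not a demonstrated bias. The Termination criteria and Blinding sections tie leaving the study to poor outcome, and the Withdrawal criteria ask for continued follow-up of the same patients. Under the assumed rates the primary difference could shift by between -4.0 and +4.4 points, with no shift if removal is equal. These figures rest on no true effect, non-response in every removed patient, and analysis of only those left. None of these is stated in the documents. The point deserves attention during recruitment because no later analysis can replace measurements that were not taken.

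**What to change.** Reword the Termination criteria and Blinding sections to agree with the Withdrawal criteria:

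1. Stopping study treatment, a non-fatal endpoint event or unblinding does not by itself end study follow-up.
2. The NT-proBNP measurements in Table 2 and endpoint-event follow-up, including death after a first non-fatal event, continue to week 24 unless the patient withdraws consent.
3. Within the Blinding section, reconcile the statement that everyone stays unaware of allocation until the study ends with unblinding on a serious adverse event.

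Decisions on treatment, and on when emergency care requires the code, are left as they are. How these patients are counted in the FAS is left to the SAP.

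The cost is a wording amendment, submitted for ethics approval as the Quality control section requires, and a few already scheduled visits kept for patients who would otherwise leave.
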